## Methods/discussion

### Setting and target population

I-TREC was developed as a collaboration between the All India Institute of Medical Sciences, New Delhi (AIIMS), the Centre for Chronic Disease Control (CCDC), and Emory University. For over a decade, these three institutions have collaboratively developed and tested the combination of information technology (IT), enhanced personnel training, and workflow alterations to improve the quality of care for diabetes and hypertension in diverse settings across India [22–29]. Most of these prior efforts focused on a single level of the healthcare system and relied on research staff to implement the intervention. In I-TREC, however, our goal was to develop and evaluate a coordinated package of tested tools and provider training approaches that catered to functions and personnel available in each type of the 4-tier healthcare system (see Table 1). We further sought to embed the program within the infrastructural scaffolding provided by the Government of India in the interest of future scalability. I-TREC was thus designed to be implemented by personnel and using resources (medications, diagnostics) already present within the public healthcare system.

**Table 1 Tab1:** Intervention components

Healthcare facility level	I-TREC components	Available Staff	Tasks and functions
**Level 1: Village Sub-Centre**	eCRF	ANM	Universal screening of hypertension and diabetes for adults ages ≥ 30 y in the community Enrol community members into the NCD portal Adults with blood pressure ≥ 140/90 or random blood glucose ≥140 mg/dl referred to medical officer at nearest facility (level 2) for confirmation and initiation of treatment
**Level 2: Primary Health Centre**	eCRF+CDSS	SN, MO	Confirmatory diagnosis of hypertension and diabetes of suspected cases referred from sub-centre Routine management of adults with stable hypertension and diabetes Generate and update eCRF Use CDSS to develop treatment plan and determine need for up-referral
**Level 3: Community Health Centre**	eCRF+CDSS	SN, MO	Run dedicated NCD clinics Routine management of adults with stable hypertension and diabetes Generate and update eCRF Use CDSS to develop treatment plan and determine need for up- or down-referral

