**Level 4: District Hospital**	eCRF+CDSS	SN, MO	Secondary care available for all health conditions and complications Management of medically complex patients with hypertension and diabetes Generate and update eCRF Use CDSS to develop treatment plan and determine need for up- or down-referral

*ANM* Auxiliary nurse midwife, *CDSS* Clinical decision support system, *eCRF* Electronic case record form, *MO* Medical officer (physician), *SN* Staff nurse

The primary implementation partners for the program include the Department of Health and Family Welfare, Government of Punjab (use of IT tools and altered work flow to deliver routine care); TATA Trusts (conduct training of healthcare workers and technical assistance); and Dell Technologies (development of software and IT infrastructure). Monitoring and evaluation activities for I-TREC will be conducted by AIIMS, CCDC, and Emory University. I-TREC will be implemented in Mukandpur block of Shaheed Bhagat Singh Nagar district, Punjab, India, and evaluated through comparison of program indictors with those observed in the neighboring Sujjon block in the same district (See Fig. 1). The program and comparison locations were selected based on consultation with the Punjab Department of Health and Family Welfare.

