#### Healthcare provider training

Healthcare providers employed in both the program and comparison blocks receive refresher content training related to the etiology, behavioral counseling, and medical management of NCDs following established NPCDCS training manuals. The content training is provided over a full day in separate sessions for auxiliary nurse midwives [ANMs], staff nurses, and medical officers. The sessions include training on effective techniques for delivering behavioral and lifestyle advice counselling. Unlike routine training, this refresher training includes innovative learning methods, such as case studies and role playing to enhance trainee engagement to assure improved comprehension and retention of behavioral and lifestyle counselling approaches. In addition, staff nurses and medical officers in the program block receive IT training on the use of the eCRF and CDSS, specific to their level of expertise and the level of healthcare facility in which they are employed.

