#### Patient flow under I-TREC

Figure 2 depicts patient flow within and across facilities in the I-TREC program. Following NHM and NPCDCS recommendations, all adults aged ≥30 years are eligible for universal screening of hypertension and diabetes in the community and opportunistic screening in health facilities by government health providers. At the village-level Sub-Centre, the lowest level of the healthcare facility hierarchy, the ANM is tasked with screening adults to identify suspected cases of hypertension and diabetes in the community. ANMs enter screening results into the “ANM portal” using a tablet-based application. Adults who are suspected to have hypertension and/or diabetes are referred to the nearest Primary Health Centre, the second level of the healthcare hierarchy, for diagnosis and treatment (see Table 1 and Fig. 2).

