**Fig. 2 Fig2:**
[figure not shown]
Patient flow under the I-TREC program. Panel **a** shows patient flow across facilities and Panel **b** shows patient flow within facilities. Figure 2 was developed by the authors

At Primary Health Centres and above—namely Community Health Centres and the District Hospital—nurses generate and update the patient eCRF through a web-based application on a computer tablet. At the time the eCRF is first generated, nurses record the patient’s clinical history. At future visits, the eCRF is updated with ongoing examination data so that the CDSS is responsive to the patient’s health status at a given visit. Patient data entered into the eCRF are uploaded to a secure cloud-based server once per day, and these data are synced and retrievable at all facilities to inform the CDSS and assist with clinical decisions.

After the initial eCRF review and update by the nurse, patients with confirmed hypertension or diabetes are instructed to see the medical officer, who is aided by the CDSS to manage these conditions. The CDSS algorithms are tailored to the expertise, medications, and diagnostic tests available at each level of facility and customized to the clinical history of the patient over all past and present contacts with the health system. Medically complex patients, such as those who are resistant to therapy, may be referred further “up” the referral hierarchy. The referral algorithms take into account a patient’s full clinical history and current health profile, including the number of medications currently prescribed, treatment response based on laboratory investigations, and comorbidities. For example, if a patient with diabetes under treatment at a PHC has uncontrolled hyperglycemia despite being on the maximum tolerated dose of three oral hypoglycaemic agents, the CDSS will trigger a referral to a CHC. Similarly, if a patient with hypertension under treatment at a CHC level has uncontrolled blood pressure despite being on the maximum tolerated dose of two antihypertensive drugs, the CDSS will trigger a referral to the District Hospital.

Once the patient achieves a stable clinical state, she or he will be referred back “down” to the lowest level of health facility (PHC or CHC) that is suitable for routine management of stable disease and dispensation of appropriate medication.

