	Proportion of diabetes patients who achieve blood glucose control in the community
**Adoption**	Proportion of healthcare providers (by type) who log into the NCD portal
	Proportion of clinicians who fully or partially accept CDSS prompts
	Proportion of healthcare providers (by type) who report satisfaction with the eCRF+CDSS
**Implementation**	Percentage of hypertension patients who received guideline-based care through the eCRF+CDSS (of all registered patients with hypertension)
	Percentage of diabetes patients who received guideline-based care through the eCRF+CDSS (of all registered patients with diabetes)
	Percentage of hypertension patients who made repeat visits to health facility
	Percentage of diabetes patients who made repeat visits to health facility
	Percentage of “up-referral” cases who attend appointments
	Percentage of patients who were seen at a higher level facility that returned to the Sub-Centre for ongoing management (“closing the referral loop” and ensuring continuity of care)
	Percentage of patients tracked with multiple visits over the course of the program
	Mean time for data upload from each level of facility to central server
**Maintenance**	Views of program sustainability and barriers to sustaining and disseminating the program (qualitative)

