### Summary

This is the first study in India evaluating the composite impact of a clinical decision support system integrated with the Government of India eCRF, combined with modified patient flow and enhanced healthcare provider training. It is also an important early effort to systematically evaluate a program for integrated management of hypertension and diabetes at all levels of the public healthcare system, starting from the sub-centre up to the district hospital. Lessons learned may inform optimal approaches to improve healthcare processes and health outcomes within the public sector healthcare system in India.

The I-TREC program and its evaluation have several strengths but also some limitations. Given the primacy of scalability, the role of research staff is limited to program design, training, monitoring and evaluation. Therefore, the context and conditions of implementation are beyond the control of investigators. For example, the availability of drugs, diagnostic investigations, and clinicians are likely to impact the reach, effectiveness, and implementation of I-TREC but rest in the hands of the state government. Nevertheless, we expect variations in these structural elements to affect both the program and comparison blocks similarly. In order to maintain comparability between the program and comparison block, neighboring blocks within the same district were chosen. However, this means that both blocks share the district hospital, which will have to be taken into account during the analysis. While we will be able to obtain patient data in the program block from the eCRF, no comparable source of data is available to use in the comparison block. Moreover, undue monitoring of the comparison block may inadvertently lead to compensation behaviors on the part of clinicians that could undermine our ability to measure performance differences across the two blocks. The community survey, in part, is designed to mitigate these limitations by providing a well-designed comparison of healthcare processes and outcomes as observed in the program and comparison blocks.

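### Table 2 scores a closed referral loop as return to the Sub-Centre, while the written patient flow and Table 1 place routine care of stable patients at a PHC or CHC

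*Protocol article*

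**What the plan says.** Under Outcomes, the protocol article presents the Table 2 indicators as the principal endpoints. One Implementation row, glossed there as closing the referral loop, is "Percentage of patients who were seen at a higher level facility that returned to the Sub-Centre for ongoing management".

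The section Patient flow under I-TREC describes the return path. Once stable, a patient is sent back down "to the lowest level of health facility (PHC or CHC) that is suitable for routine management of stable disease". At the Sub-Centre, "the ANM is tasked with screening adults to identify suspected cases of hypertension and diabetes in the community", and suspected cases go on to the PHC.

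Table 1 sets out tasks by level:

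- **Level 1, Sub-Centre:** screen, enrol in the portal, refer suspected cases to Level 2.
- **Level 2, PHC:** "Routine management of adults with stable hypertension and diabetes", and "Use CDSS to develop treatment plan and determine need for up-referral".
- **Level 3, CHC:** the same routine-management task, and "Use CDSS to develop treatment plan and determine need for up- or down-referral".
- **Level 4, District Hospital:** medically complex patients, with the same two-way referral task as Level 3.

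On the minor point, Table 2 has two control rows for facility patients: one joins blood pressure and glucose control, the other is glucose control alone. The community rows treat blood pressure control and glucose control separately.

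**The concern.** The indicator and the intervention name different destinations. An analyst who applies Table 2 literally would look for a Sub-Centre visit after a higher-level visit. A clinician who follows the written flow would send the stable patient to a PHC or CHC. The patient then enters the denominator but not the numerator.

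This matters because referral and care coordination are named parts of the program, and this is the only Table 2 row about return down the hierarchy. The neighbouring row covers attendance after up-referral only. A pathway that worked as described could therefore be reported as one that did not.

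The smaller concern is that a facility patient with hypertension but no diabetes has no control indicator that clearly applies, although the community set provides one.

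**Working it through.** The plan gives no figure to reproduce, so the check sets the texts side by side.

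**Where stable disease is managed.** Table 1 lists routine management at 2 of 4 levels (PHC and CHC). The Sub-Centre has three tasks, none of them management. The flow text agrees and names the PHC or CHC in its parenthesis.

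**Whether any step leads down to a Sub-Centre.** Table 1 lists a down-referral decision at 2 of 4 levels (CHC and District Hospital) and only an up-referral decision at the PHC. Table 1 does not name the destination of a down-referral; the flow text does, and the Sub-Centre is not among the destinations.

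**Whether a Sub-Centre management visit would be recorded.** The flow text has Sub-Centre auxiliary nurse midwives (ANMs) entering screening results in a separate ANM portal, and nurses generating and updating the electronic case record form (eCRF) at the PHC and above. Under Healthcare provider training, "staff nurses and medical officers in the program block receive IT training on the use of the eCRF and CDSS". No capture of a follow-up visit at Level 1 is described.

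**How typical paths would be scored:**

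| Path | Written flow | Table 2 as worded | Row as proposed under fix |
|---|---|---|---|
| PHC to CHC, stabilised, referred to and attends PHC | correct | failure | success |
| CHC to District Hospital, stabilised, referred to and attends CHC | correct | failure | success |
| Complex patient properly kept at District Hospital | correct | failure | not in denominator |
| PHC patient referred up and properly kept at CHC | correct | failure | not in denominator |
| Referred down, does not attend | loop not closed | failure | failure |

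As worded, the row puts all five paths in one category, although only the last is a failure of the pathway. The third and fourth lines show why changing the destination alone would not be enough. With the denominator kept, properly retained patients would still count as failures, or a patient retained at a CHC could be counted as having returned to one.

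**Extent.** Table 2 has 3 Reach + 8 Effectiveness + 3 Adoption + 8 Implementation + 1 Maintenance = 23 rows. The loop row is 1 of the 8 Implementation rows. The minor point concerns one indicator missing from the Effectiveness set, where the facility control rows include 0 for blood pressure alone and the community rows include 1.

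**The case against.** A coherent alternative reading exists. The referral chain starts at the Sub-Centre, so closing the loop could mean return to the point of origin for community follow-up, with prescribing left to the PHC or CHC. Several things fit this. ANMs receive the one-day content training, which covers counselling and medical management. Table 1 lists the eCRF as the Level 1 component. The Summary describes integrated management "starting from the sub-centre up to the district hospital". Fig. 2, which shows the flow across facilities, is not reproduced in the text at hand, and the full protocol may define the row more closely.

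This stands as a possibility, and it is why the direction of error is conditional. It does not remove the conflict: no shown text gives the Sub-Centre a follow-up task, and the Summary phrase is satisfied by screening. If the alternative is what was meant, the flow text and Table 1 need the correction.

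The weight is also fairly challenged. This is one indicator with no stated hypothesis or power. The Statistical analysis plan section focuses the quantitative evaluation on the community surveys and calls several platform indicators purely descriptive. The label of principal endpoint covers the whole table and gives this row no special rank.

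On the minor point, joint control may be deliberate in an integrated program, and facility mean blood pressure keeps its own row. That argues for adding a row and against replacing the joint one.

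**Conclusion.** The inconsistency is real and should be settled before the indicator is analysed. Its weight is modest: the wording of one descriptive row, plus one row probably missing through a drafting slip.

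That the row understates return after up-referral rests on one assumption, namely that the written patient flow is the intended one. The size cannot be computed, because the documents give no numbers of patients referred up, referred down or returning.

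A reader might infer that the indicator is bound to come out near zero. The documents do not support that: some patients may visit a Sub-Centre after higher-level care, and no rate is given. A reader might also infer that the effectiveness evaluation is compromised. It is not: the sample sizes, the difference-in-difference model and the community endpoints do not use this row. Nor do the documents show that Sub-Centre follow-up is ruled out; they only do not describe it.

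**What to change.** **Main point.** Redefine the row as: the percentage of patients seen at a CHC or the District Hospital, and then referred down by the decision support system or the clinician, who attend the lower-level PHC or CHC to which they were referred, as recorded in the eCRF. This corrects the destination, states what higher level means, and takes properly retained patients out of the denominator.

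If follow-up at the Sub-Centre is intended, leave the destination in Table 2. Amend the down-referral sentence in Patient flow under I-TREC and add the follow-up task, with the way it is recorded, to Level 1 of Table 1.

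**Minor point.** Add a facility row for blood pressure control among patients with hypertension, parallel to the community row. Keep the joint row if it is wanted.

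**Cost.** One row reworded and one added. No new collection should be needed. The article says that referral instructions become part of the patient's eCRF, that the eCRF is updated at the PHC and above, and that its data can be retrieved at all facilities. This assumes that the referral destination is stored in a form that can be matched to later visits, which should be checked when the row is revised.

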#### Sources of data for evaluation

Data will be triangulated from multiple sources, including facility and patient assessments, stakeholder interviews, community surveys, and patient-level data from the I-TREC electronic database. Where appropriate, data will be collected prior to the program launch and again following 36 months of the program. With the exception of the I-TREC eCRF-CDSS data, evaluation data will be collected by trained research staff.

#### Health facility and patient assessments

Pre- and post-program health facility and patient assessments include 1) a health facility form; 2) patient flow mapping; and 3) patient out-of-pocket cost of care surveys. Health facility forms will be completed at all 52 government health facilities (21 in program and 30 in control and the common District Hospital) to describe the infrastructure, facility personnel and salaries, availability of medications, and availability of diagnostics and laboratory investigations. Health facility form completion requires a combination of observational checklists and structured interviews with administrators. Patient flow mapping entails identifying and following patients with hypertension and diabetes through typical visits to map the typical workflow, diagnostic and prescription practices, and duration of visits. Together, the health facility form and patient flow mapping will provide data to describe the resources (time and costs) associated with typical healthcare visits for patients with hypertension and diabetes with and without the I-TREC program. Patient cost surveys will be used to obtain data on expenditures related to outpatient and inpatient health care utilization in the last 3 months to understand the cost incurred by patients to manage their disease. Administration of the pre- and post-program patient cost surveys will contribute data to understand whether the program has any impact on patient expenditures related to hypertension and diabetes. Purposive sampling will be done to recruit patients for the patient flow mapping and cost surveys.

#### Stakeholder perspectives

Qualitative methods will include a combination of focus group discussions of the community members, key informant interviews with healthcare providers and in-depth interviews of patients to provide a richer interpretation of quantitative findings and explore the processes underlying the uptake and delivery of the I-TREC program. The qualitative research will be conducted before, during, and after program implementation. Purposive sampling will be done to recruit information-rich participants for interviews and focus group discussions. For all qualitative data analysis, the textual data (verbatim transcripts created from digital recordings of interviews and focus group discussions) will be reviewed to identify key themes and domains of interest. A code book will then be developed to reflect these domains and include both inductive (derived from the textual data) and deductive (based on literature and theory) codes. Inter-coder reliability will be assessed, and the codebook will be finalized and applied to the data. The codebook will include codes specific to each type of data collection and shared codes across participant type. A thematic analysis will be used to describe individual- or community-level views on discussion topics including program barriers and facilitators, community barriers, views of the healthcare system, and acceptability and feasibility of the program.

#### Pre- and post-program quantitative cross-sectional community surveys

The community-based evaluation component will assess whether the I-TREC program has an impact on blood pressure and blood glucose awareness, treatment seeking, and control among adults in the community. This evaluation component is critical to learning the real-world impact of the I-TREC program on community-level indicators of the care continuum (screening, treatment, control). Data collected in the program and comparison blocks prior to the program will be compared with data collected from these same blocks after the program using identical procedures. This design allows us to assess and address several threats to validity, including lack of temporal order, comparability across the two blocks (leading to potential confounding by population composition) and secular changes unrelated to our program that affect study endpoints (leading to potential confounding by external factors). Given that we will be sampling separate cross-sections of the population in each group and time point, we do not expect inference to be affected by population aging (maturation threats) over the 3-year program period.

At baseline—prior to intervention—we employed a multi-stage cluster sampling design to obtain a representative sample of adults aged 30 years and older in both blocks under study. Within each block, census data were used to select villages proportionate to population size and subsequently we conducted household mapping and listing to generate a sampling frame for households. Households were selected using systematic random sampling, and one adult man and woman from each household were randomly selected using the Kish method to achieve the desired sample size. At endline, this same procedure will be repeated.

The community survey sample size was determined to estimate differences in mean reduction in systolic blood pressure among those with diagnosed hypertension in the community. First, we computed the base sample size required to detect a desired effect size of 5 mmHg given the SBP standard deviation of 18.5, power = .80 and α = .05, based on the mPower Heart Study [24]. We estimated that 168 individuals with hypertension would be needed to detect the anticipated effect size. Second, we estimated that we would require a sample size of 839 adults in the general population to identify 168 individuals with hypertension, assuming prevalence of diagnosed hypertension of 20%. Third, we determined the optimal sample allocation for a multi-stage sampling design that would be time-efficient for field work and statistical precision. We assumed an intraclass correlation of systolic blood pressure of 0.018 based on village-level clustering of SBP in the DISHA study [32] (unpublished findings). After applying a 10% refusal rate based on our prior field studies in the region, we determined that a cluster size of 50 adults per village distributed across 35 villages per block was optimal. This yielded a total sample size of 3508 for the community survey to be evenly split between the program and comparison blocks.

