The coefficient associated with the interaction term, “program group x pre-post indicator,” is the adjusted DiD estimate accounting for heterogeneity in socio-demographic characteristics. The model will be estimated using generalized estimating equations (GEE) to account for clustering of outcomes within the villages (i.e. village is the cluster variable specified for statistical analysis). Sub-group analyses will examine differences by gender and socioeconomic status.

Data points recorded in the I-TREC system will be analyzed by month to examine trends over time and seasonality. We will also evaluate change patient outcomes over time (e.g., mean SBP change). While several of the I-TREC platform indicators are purely descriptive measures of performance (e.g., mean time for data upload), other indicators of healthcare delivery may be compared between I-TREC facilities and comparison group facilities (e.g., patient volume).

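### Read literally, endline repeats the village draw; keeping the 35 baseline villages per block would be a cheap gain in difference-in-difference precision, not the cure of a bias

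*Protocol article*

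**What the plan says.** All references are to the protocol article.

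- **Baseline sampling** (section on the pre- and post-program community surveys). "Within each block, census data were used to select villages proportionate to population size". Household listing, systematic household sampling and Kish selection of adults follow.
- **Endline sampling** (same section). "At endline, this same procedure will be repeated". The text does not say whether the baseline villages are revisited. It states that the same two blocks are compared, which fixes the blocks but not the villages.
- **Independence of rounds** (same section). The design rationale begins "Given that we will be sampling separate cross-sections of the population in each group and time point". This concerns people and fits either reading on villages.
- **Sizing** (same section). The survey is sized for "differences in mean reduction in systolic blood pressure among those with diagnosed hypertension in the community", with a "desired effect size of 5 mmHg given the SBP standard deviation of 18.5" and "power = .80 and α = .05". The village ICC is 0.018, refusal is 10%, and there are 35 villages per block with 50 adults each.
- **Analysis** (Statistical analysis plan). The DiD is the group-by-period interaction in a GEE, and "village is the cluster variable specified for statistical analysis".

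**The concern.** The DiD compares four block-by-round means. If the same villages contribute before and after, whatever is stable about a village (access to a clinic, diet, wealth) appears in both rounds and subtracts out. If endline uses other villages, that variation enters each round independently and stays in the variance of the DiD. The adjustment covariates are individual characteristics plus facility type. There is no village term that would do the same job.

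What is at stake is the width of the confidence intervals for the community indicators. The village share of the variance grows with the number of respondents per village. It is therefore small for diagnosed hypertensives and larger for anything measured in every sampled adult.

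**Working it through.** **1. The plan's own total.** Design effect: 1 + (50 − 1) × 0.018 = 1.882. Per block: 839 × 1.882 / 0.9 = 1,754.4. Two blocks: 3,508.9, which matches the stated 3508.

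**2. Respondents per village (m) and per block and round (n).**
- All adults: 50 × 0.9 = 45 per village; n = 35 × 45 = 1,575.
- Diagnosed hypertensives at 20%: 45 × 0.2 = 9 per village; n = 35 × 9 = 315.

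**3. Formula.** Let ρ be the ICC and r the cluster autocorrelation, that is, the correlation of a village's underlying level between rounds.

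Var(DiD) = 4 × SD² × D / n
- Different villages: D = 1 + (m − 1)ρ
- Same villages: D = 1 + (m − 1)ρ − r·m·ρ

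The article gives no r, so 0.5, 0.8 and 1 are assumptions. SD = 18.5 and ρ = 0.018 are the plan's. Two-sided power at 5 mmHg is Φ(5/SE − 1.96).

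**4. Results, assuming no village falls in both draws.**

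| Population | Villages | D | SE (mmHg) | Variance cut | Power at 5 mmHg |
|---|---|---|---|---|---|
| Hypertensives, m = 9 | different | 1.144 | 2.23 | – | 61% |
| | same, r = 0.5 | 1.063 | 2.15 | 7% | 64% |
| | same, r = 0.8 | 1.014 | 2.10 | 11% | 66% |
| | same, r = 1 | 0.982 | 2.07 | 14% | 68% |
| All adults, m = 45 | different | 1.792 | 1.248 | – | |
| | same, r = 0.5 | 1.387 | 1.098 | 23% | |
| | same, r = 0.8 | 1.144 | 0.997 | 36% | |
| | same, r = 1 | 0.982 | 0.924 | 45% | |

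A simulation of the hypertensive case gave SEs of 2.231, 2.098 and 2.058 for different villages, r = 0.8 and r = 1, in line with the formula.

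The percentage cut does not depend on the SD, so the all-adult rows carry over to a screening proportion if its ICC were also 0.018. If it were 0.05 (an assumption), m·ρ = 2.25 and D = 1 + 44 × 0.05 = 3.2 with different villages. The cut would then be 0.5 × 2.25 / 3.2 = 35% up to 2.25 / 3.2 = 70%.

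**5. Chance overlap between two draws.** If a fraction q of villages is reselected and shares its identifier across rounds, the redraw has D = 1 + (m − 1)ρ − q·r·m·ρ. The article does not give the number of villages per block. Simulated draws proportional to size, with assumed village sizes, gave q of about 43%, 59% and 92% for blocks of 120, 80 and 40 villages. At r = 0.8:

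| Overlap q | All adults: D of redraw | Cut from keeping villages | Hypertensives: D of redraw | Cut |
|---|---|---|---|---|
| 0 | 1.792 | 36% | 1.144 | 11% |
| 43% | 1.792 − 0.43 × 0.648 = 1.513 | 24% | 1.144 − 0.43 × 0.1296 = 1.088 | 7% |
| 59% | 1.410 | 19% | 1.068 | 5% |
| 92% | 1.196 | 4% | 1.025 | 1% |

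The power gain for hypertensives shrinks from about 5 points to about 3, 2 and under 1.

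**6. Why the starting power is 61% and not 80%.** This is a separate matter. The plan's 168 is close to a one-sided comparison of two means, 2 × (18.5 × (1.645 + 0.842)/5)² = 169.3; the two-sided figure is 215. It also does not allow for four cells. The village draw explains little of the gap: even at r = 1, power is only 68%.

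**The case against.** **The redraw is inferred.** The article neither says that villages are redrawn nor that they are kept, and a full protocol exists that is not shown. This stands as a caution. However, the village draw is the first step of the procedure to be repeated, so the literal text includes it, and the same clarifying sentence is needed if the sponsor means to revisit the villages.

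**The larger figures may not apply to blood pressure and glucose.** A reader might take community mean blood pressure and glucose in Table 2 as all-adult indicators and claim the 23–45% for them. The Outcomes section describes community effectiveness among adults with hypertension and/or diabetes. The Statistical analysis plan is looser but does not say all adults. Only the two screening proportions are clearly all-adult, and no ICC is given for them. This stands.

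**The gains are upper bounds.** Chance reselection reduces them, in a small block to almost nothing. The compositional covariates may also absorb some village variation that the unadjusted formula ignores. Both stand.

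**There is no bias.** A reader might infer that chance differences in which villages are drawn could pass for a program effect. The documents do not support that. Both draws are probability samples of the same blocks, and the village-clustered GEE with robust variance carries village sampling variation into the standard error.

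**Conclusion.** The point holds as one of precision and clarity. As written, the endline repeats the village draw, and to the extent that the villages differ, stable village variation does not cancel in the DiD. For the outcome on which the survey was sized, the loss is modest: at most 7–14% of the variance, or 3 to 7 points of power. For all-adult indicators it could reach 23–45%, on the condition that the ICC of 0.018 applies.

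These sizes rest on an assumed cluster autocorrelation of 0.5–1 over 36 months and on no overlap between draws. With overlap they shrink as shown, but retention lowers the variance at any positive autocorrelation unless every village is reselected anyway.

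It would go too far to say that keeping the villages removes most of the village variation. That needs an autocorrelation above 0.5, which the article does not give. Nor is it entirely free of cost.

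**What to change.** State in the endline survey procedure that the survey returns to the same 35 baseline villages per block, with fresh household listing and a new random draw of households and adults. This preserves separate cross-sections of people. Give each village one identifier across both rounds, so that its pre and post observations fall in the same GEE cluster; otherwise the standard error will not reflect the gain. If the sponsor prefers a new village draw, say so and give the reason.

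The cost is a sentence and a common identifier. No extra interviews are needed, and household listing is already part of the procedure to be repeated. The baseline survey is complete, so the village list should exist. The small downside is that some residents may have met the baseline survey, which should apply similarly in both blocks.
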